HR Heart rate
IMP Investigational medicinal product
IP In-plane needle guidance technique
IRB-IEC Institutional Review Board – Independent Ethics Committee
i.v. Intravenous
JPEG Joint Photography Expert Group
NSAID Non-Steroidal-Anti-Inflammatory-Drug
OTC Over the counter
PD Pharmacodynamic
PK Pharmacokinetic
PTT Partial thromboplastin time
RBC Red blood count
SUSAR Suspected Unexpected Serious Adverse Reaction
t_1/2_ Termination elimination half-time
t_max_ Time to maximum concentration
WBC White blood count

# Synopsis

| TITLE | **The Impact of Biological Gender in Peripheral Nerve Blockade: A Prospective Study in Volunteers** |
| --- | --- |
| Phase | IV |
| INVESTIGATIONAL PRODUCTS | **Drug:** Ropivacaine  ***Concentration:*** 7.5 mg/mL (0.75%) |
| BACKGROUND | To evaluate PD, PK and nerve-related morphometric differences of biological gender (male versus female) on nerve block characteristics |
| OBJECTIVES | **Primary Objective**   - Duration of sensory nerve blockade   **Secondary Objective**   - Pharmacokinetic characteristics (C_max_, t_max_, t_1/2_, AUC_0-6_, AUC0-∞) - Duration of motor blockade - Onset time of sensory nerve blockade - Onset time of motor blockade - Diameter of the ulnar nerve (absolute and relative to the BMI) - Visibility of the ulnar nerve in ultrasound (Grey-tone analysis ulnar nerve relative to the surrounding tissue) |
| DESIGN | Prospective, single-centre, interim-analysis after 2 x 12 cases |
| HYPOTHESIS | Null-hypothesis: biological gender (male or women) does not influence the primary outcome variable  Alterative-hypothesis: biological gender (male or women) influences the primary outcome variable |
| CONTRIBUTION TO THE CLINICAL PRACTICE | In the case of rejection of the null-hypothesis, peripheral regional anaesthesia techniques can be adapted to the particular biological gender and PD characteristics can be adapted to the respective clinical indication. |
| BLINDING-PROTOCOL | - |
| CENTER(S) / COUNTRY(IES) | 1 centre in Austria (Department of Clinical Pharmacology, Medical University of Vienna) |
| PATIENTS / GROUPS | 45 healthy male and 45 healthy female volunteers (total number of volunteers: 90). An interim-analysis will be after 12 male and 12 female volunteers. |
| INCLUSION CRITERIA | - Healthy males and females - Healthy, according to the medical history, ECG, vital signs, laboratory results and physical examination as determined by the Investigator/Sub-Investigator - Signed written informed consent prior to inclusion in the study - 18-55 years old inclusive - BMI: 18 to 35 kg/m^2^ - Ability to understand the full nature and purpose of the study, including possible risks and side effects - Ability to co-operate with the investigator and to comply with the requirements of the entire study - Availability to volunteer for the entire study duration and willing to adhere to all protocol requirements |
| EXCLUSION CRITERIA | - Any clinically relevant abnormalities at ECG (12 leads) - Any clinically relevant abnormal physical findings - Any clinically relevant abnormal laboratory values indicative of physical illness - Ascertained or presumptive hypersensitivity to the active principle and/or formulations ingredients of the study drug - History of anaphylaxis to drugs or allergic reactions in general, which the investigator considers may affect the outcome of the study - Relevant history of malignancy, of renal, hepatic, cardiovascular, respiratory, gastrointestinal, musculoskeletal, skin (particularly at the site of drug application), haematological, endocrine or neurological diseases that may interfere with the aim of the study - Pregnancy - Any psychiatric illnesses - Any anticoagulatory or pain-therapy-related drugs (e.g. NSAIDs, opioids) from one week before until the end of the study - Using other medications during 1 week before the start of IMP application including OTC - Participation in another clinical study investigating another IMP within 1 month prior to screening - Blood donations during 4 weeks prior to this study - History of drug or alcohol abuse - Other objections to study participation in the opinion of the investigator |
| STUDY PROCEDURES | A screening visit precedes the first study day. Each volunteer will undergo one ulnar nerve blockade. For each individual, duration of the whole study (including screening and end-of-study visits) will be two weeks. The duration of the active study participation is estimated between 8 and 12 hours.  Once inclusion criteria are fulfilled and written informed consent to study participation is provided, participants will be asked to report at the study centre on the study day at a convened time.  Volunteers receive one ulnar nerve block (description of standardized performance of blockade see below) on the non-dominant side according to one of the two study groups. Evaluation of sensory blockade will be performed via Pinprick testing (method and timing of evaluation see below). Evaluation of motor blockade will be performed via the evaluation of thumb adduction (method and timing of evaluation see below).  Venepuncture blood draws will be performed throughout a vascular access for evaluation of pharmacodynamic characteristics.  Ultrasonographic appearance (visibility) of the ulnar nerve will be detected via grey scale analysis. |
| ADMINISTRATION OF STUDY DRUGS, STUDY GROUPS | **Study group M:** **M**ale volunteers receive 3 mL Ropivacaine 0.75% (7.5 mg/mL = 22.5 mg/mL) perineural to the ulnar nerve  **Study group F:** **F**emale volunteers receive 3 mL Ropivacaine 0.75% (7.5 mg/mL = 22.5 mg/mL) perineural to the ulnar nerve  Ulnar nerve blocks will be performed under sterile conditions via ultrasound guidance at the middle third of the forearm (exact definition see below). |
| ASSESSMENT OF BLOCKADE | Sensory blockade will be evaluated via Pinprick testing (0 = no sensory feeling, 100 = no difference in sensory feeling to the corresponding non-blocked side) at the hypothenar area compared with the corresponding non-blocked side.  Motor blockade will be evaluated via adduction of the thumb:  3 = no difference, adduction against contra-force possible  2 = slight difference, adduction against slight contra-force hardly possible  1 = significant difference, adduction without contra-force hardly possible  0 = no active adduction possible, paralysis |
| PHARMACOKINETIC PARAMETER | - Maximum concentration (Cmax) - Time to maximum concentration (tmax) - Terminal elimination half-life (t1⁄2) - Area under the concentration–time curve (AUC) for the sampling period of 6 h (AUC0-6) - The total AUC (AUC0-∞). |
| ULTRASOUND VISIBILITY | Difference of grey scale analysis between the median grey scale of the cross-sectional area of the ulnar nerve and areas of a similar ulnar nerve size in a 0, 3, 6 and 9 o´clock position  $Grey Scale Value Ulnar Nerve/\frac{Grey Scale Values 0,3,6,9 o´clock}{4}$  Vienna Scoring System:   1. Internal Structure of the nerve visualized 2. The nerve is visualized as a circular or oval-shaped blight halo (epineurium) 3. The nerve is visualized as reflection determined by the anatomy of the surrounded tissue 4. The anatomical position of the nerve shows no response to the ultrasound beam (isoechoic behaviour) |
| HOUSING | On study days, subjects will be confined at the clinic until the percentage of Pinprick testing is back to 20 and motor blockade back to 1. For the whole duration of their stay, they will be under constant medical supervision. |
| POWER ANALYSIS | A previous study with ropivacaine 0.75% for ulnar nerve blockade showed a duration of sensory blockade of 350 min with the largest SD of 54 minutes.^2^ We expect a true difference of approximately 35 minutes (10%). Assuming a true difference in means between the study groups of 35 minutes, a pooled standard deviation of 54 minutes, the study would require a sample size of 38 for each group (i.e. a total sample size of 76, assuming equal group sizes), to achieve a power of 80% and a level of significance of 5%. For nonparametric analysis, the sample size is increased by 15% to *90* subjects.  After 2 x 12 cases, we perform an interim-analysis to re-evaluate the number of initially calculated subjects. A subsequent power-analysis will be performed to determine the definitive number of study cases. We intend to achieve a power of 80% and a level of significance of 5% to find a nominal difference of 10 to 15%.  Interim analyses and sample size calculations will be conducted using the O’Brien-Fleming alpha spending function for test boundaries in PASS and NCSS software (NCSS Inc., Kaysville UT.) |
| STATISTICAL METHODOLOGY | Pharmacodynamic data analysis: The primary outcome is duration of sensory block. Secondary outcomes include onset of sensory block, onset and duration of motor block.  Data will be presented as mean (SD), median [interquartiles] and count (%) and analysed using unpaired two-sided Student *t-*, Mann-Whitney *U-*, log-rank and Fisher exact statistics. The primary outcome will be analysed using unpaired Student *t-*, Mann-Whitney *U-* or log-rank statistics as appropriate. Secondary analyses will include mixed effects linear models to adjust for subject and baseline characteristics and for repeated measures in subjects as random intercepts.  Pharmacokinetic data analysis: Secondary outcomes, including parameters such as C_max_, t_max_and AUC will be estimated and analysed using statistics as listed above.  Morphometric data analysis: Differences between grey scales of nerves and nerve visibility (differences between nerves and surrounding tissue) and differences in the Vienna Scoring System will be compared using unpaired two-sided Student *t-* or Mann-Whitney *U-* statistics as appropriate. Mixed effects linear models will be performed to determine the correlation of nerve visibility with morphometric variables. |

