## Assessment of sensory and motor blockade

*Sensory blockade* will be assessed via Pinprick testing (100 = no difference to the contralateral side, 0 = no sensory reception) at the hypothenar area in comparison with the contralateral side. Five areas of sensory supply are defined:

- dorsal side hypothenar muscles
- ulnar side hypothenar area
- palmar side hypothenar muscles
- fifth finger
- ulnar side fourth finger.

Short bevel needles are used for Pinprick testing. The tip of the needle will be applied with a force adequate to indent the skin without puncturing it, and this will produce a consistent painful sensation when applied to non-blocked areas. This kind of sensory testing is well described in the literature.^2,13^ Evaluation of skin temperature (which is also a factor of skin-sensitivity) will not be performed because of conflicting results in the literature and various factors influencing the measurements.^22^ In addition, the sympathetic portion of the ulnar nerve is unpredictable (different to e.g. the sciatic nerve, where a large portion of sympathetic fibres can be assumed).^23^

*Motor blockade* will be assessed via adduction of the thumb:

- 3 = no difference, adduction against contra-force possible
- 2 = slight difference, adduction against slight contra-force hardly possible
- 1 = significant difference, adduction without contra-force hardly possible
- 0 = no active adduction possible, paralysis

Sensory and motor testing will be performed at the following time points (min):

Baseline, 2, 4, 6, 8, 10, 15, 20, 30, 60 min after the block, and then every 30 min until Pinprick testing = 80 and motor-scale = 1.

*Onset of sensory and motor block* is defined as Pinprick = 0 in the hypothenar area (4 from 5 above-described areas to consider anatomical variations) and motor scale = 0.

Duration of sensory and motor block is defined as Pinprick testing = 80 in the hypothenar area and motor scale = 1.

We decided to define sensory block duration when Pinprick testing = 80 (and not back to 100) to avoid an extreme long duration of investigation. According to previous results with ropivacaine 0.75% (7.5 mg/ml), the duration of complete recovery from sensory block can be estimated with > 6 hours.

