## Study day

In the morning of the study day volunteers will be admitted to the clinical research ward which they will not leave until return of sensory and motor function (definitions see below).

The volunteers will receive a plastic cannula (Venflon®) with a switch-valve inserted into an antecubital vein for iv. administration of emergency drugs (in case of hypotension or bradycardia). Thereafter the nerve blocks will be performed as described elsewhere. Each volunteer will receive one ultrasound guided ulnar nerve block on the non-dominant arm.

The sensory evaluation of the nerve block will be assessed with Pinprick testing. The motor evaluation of the nerve block will be assessed by adduction of the thumb.

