## Definition of duration of blockade

### Sensory blockade

Time from Pinprick = 0 to Pinprick = 80

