### Motor blockade

Time from motor score = 0 to motor score = 1

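### The synopsis Housing row lets confinement end at Pinprick 20, although testing and the primary endpoint run to Pinprick 80; the 20 is probably a drafting error

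*Protocol*

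**What the plan says.** The Housing row of the protocol synopsis sets the end of confinement: "subjects will be confined at the clinic until the percentage of Pinprick testing is back to 20 and motor blockade back to 1".

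The body of the protocol uses a different sensory threshold:

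- Assessment of sensory and motor blockade continues testing "every 30 min until Pinprick testing = 80 and motor-scale = 1". It also explains the choice of threshold: "We decided to define sensory block duration when Pinprick testing = 80 (and not back to 100"), so that the observation period does not become too long.
- Definition of duration of blockade gives, for the sensory block, "Time from Pinprick = 0 to Pinprick = 80" and, for the motor block, "Time from motor score = 0 to motor score = 1".
- Study day admits volunteers to the research ward, "which they will not leave until return of sensory and motor function (definitions see below").
- Time points, under Methods, repeats the testing schedule but ends it at full recovery, with no number.

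The synopsis does not claim to be complete on this subject. Its Study Procedures row says "Evaluation of sensory blockade will be performed via Pinprick testing (method and timing of evaluation see below"), and it adds: "The duration of the active study participation is estimated between 8 and 12 hours".

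**The concern.** Duration of sensory block is the primary outcome. It is observed only if someone tests the volunteer in person until Pinprick reaches 80. A rule that lets volunteers go at an earlier stage of recovery conflicts with that.

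The Housing row is also the only place where a threshold for leaving is written directly as a number; Study day sets it by reference to later definitions. Someone working from the synopsis alone would take 20 as the rule.

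Used that way, it could have two consequences. A volunteer could go home with sensation in the ulnar area still far from normal. The reading that ends the primary endpoint would also be missing for anyone released between 20 and 80. Whether it was missing would then depend on how slowly the block wore off, which is the quantity being compared between men and women.

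**Working it through.** No formula applies and the plan has no figure to reproduce. The check is a comparison of the sections.

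**1. Direction of the scale.** The synopsis and the Assessment section both give 0 for no sensation and 100 for no difference from the other hand. Recovery runs upward, so 20 precedes 80. At 20 the volunteer reports 20/100, one-fifth of normal sensation, and 80 − 20 = 60 scale points remain before the endpoint is reached.

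**2. The thresholds side by side.**

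| Place in the protocol | What it governs | Sensory | Motor |
|---|---|---|---|
| Synopsis, Housing | end of confinement | 20 | 1 |
| Assessment of sensory and motor blockade | end of testing; duration | 80 | 1 |
| Definition of duration of blockade | duration | 80 | 1 |
| Study day | leaving the ward | return of function, defined later | return of function, defined later |
| Time points | end of testing | full recovery | full recovery |

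The motor value in the Housing row agrees with the body wherever the body gives a number. Only the sensory value is out of line, and 20 is used as a Pinprick threshold nowhere else.

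**3. What Study day points to.** No later section is headed return of function. The numeric recovery definitions that follow are those for duration, ending at 80 and 1. Reading Study day as 80 and 1 is therefore an inference, though the natural one. Time points also follows and would point to a still later moment. Neither reading leads to 20.

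**4. Can both rules be obeyed?** Yes. Housing sets a period of confinement; it does not order discharge or stop the testing. Keeping a volunteer until 80 satisfies Housing, Assessment and Study day together. An endpoint is lost only if 20 is treated as permission to leave.

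**5. Would anything else protect the endpoint in that case?** The last blood sample is due at 360 min (Pharmacokinetic Analysis), which keeps volunteers on site until then. The planning mean for sensory duration is 350 min with an SD of 54 min, and the Assessment section expects complete recovery to take more than 6 hours. The 360-min sample is therefore no guarantee that 80 has been reached. The follow-up under Final examination is a telephone interview up to 7 days later, which cannot supply a Pinprick reading.

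**The case against.** The best defence is that the protocol already prevents the harm. Assessment requires testing to 80, Study day keeps volunteers on the ward until function returns, Time points goes further still, and an estimated 8 to 12 hours of participation fits a stay well past early recovery. The synopsis itself defers to the body for how and when Pinprick is tested. Staff would have to apply one synopsis row against several body instructions before a reading was lost. This stands, and it is why the point is minor.

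A second objection is that the body is not uniform either, because Time points ends testing at full recovery rather than at 80. That is correct. It means the correction should cover that section too, but it gives no support to 20, which conflicts with full recovery as well.

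A reader might also infer that the plan will lose a calculable share of its primary endpoints, for instance by using the 350-min mean and 54-min SD to find how many volunteers are still short of 80 at a chosen clock time. The document does not support that step. Such a share would be the same if the row said 80, so it does not measure the error. The relevant quantity is the number of volunteers who would leave between 20 and 80, and the protocol gives no information on how long that interval lasts. Nor does it say whether the 350 min was counted from injection or from onset, or to which threshold.

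**Conclusion.** The Housing row is wrong as written, and the point is minor. It is an operating threshold that disagrees with the end of testing, the definition of the primary endpoint and the ward rule. That 20 is a drafting slip is an inference, but a well-supported one: the motor half of the sentence matches the body, 80 is the only other number given, and the body states a reason for choosing it.

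The effect depends on conduct. If Assessment and Study day are followed, no endpoint is lost. If 20 were used as the discharge rule, volunteers with motor score 1 could leave before the endpoint is observed, and it could not be recovered afterwards. How many cannot be estimated from the document. It would be wrong to conclude that the protocol orders discharge at 20, or that the primary endpoint as defined is compromised; the text supports neither.

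**What to change.** 1. In the synopsis Housing row, replace the Pinprick value of 20 with 80, as defined for sensory block duration in Assessment of sensory and motor blockade and in Definition of duration of blockade. A reference is better than restating the tested areas: the four-of-five-areas rule is given only for onset, and the row should not extend it to recovery.
2. Add one sentence: discharge may not precede the recorded Pinprick reading of 80 and motor score 1.
3. In Time points, replace full recovery with the same end point, so that testing ends at one stated place throughout.

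The cost is one number, one sentence and one aligned phrase. Sample size, visits, blood sampling and the 30-minute testing intervals do not change.

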# Introduction

The importance of regional anaesthesia in perioperative medicine is increasing. Regional anaesthesia (with or without sedation / general anaesthesia) is the method of choice regarding optimized pain therapy, decreases or even avoids the quantitative demand of perioperative opioids, and is associated with non-pain related effects. Improved postoperative gastrointestinal function, decreased need of postoperative mechanical ventilation, less postoperative nausea and vomiting or less postoperative confusion are only a few non-pain related effects of regional anaesthesia.

Regional anaesthesia is in principle subclassified in central and peripheral regional techniques. Central regional anaesthesia is the umbrella term for neuraxial regional techniques, where local anaesthetics are administered in the epidural (epidural anaesthesia) or subarachnoid (spinal anaesthesia) space. Peripheral regional anaesthesia is the technical term for blockade techniques of single nerves or complex nerval structures (e.g. the brachial plexus). Ultrasonographic guidance enables a precise administration of local anaesthetic drugs around nerve structures (extra-epineural), which is associated with an excellent margin of safety (= avoidance of intraneuronal or intravascular puncture) and improved pharmacodynamic nerve-block characteristics (= improved sensory and motor nerve-blocks as compared with other techniques of nerve detection).

In 1993, Kapral et al. identified the use of ultrasound for regional anaesthesia purposes, where nerve structures, adjacent anatomical structures, the cannula and the spread of local anaesthetic solutions could be directly visualized. With the further development of ultrasound technology and an increased knowledge ultrasound guided regional anaesthetic techniques, success rates and the usage in the daily clinical practice increased worldwide. Nowadays challenges in the context of regional anaesthesia are the facts that no new specific drugs are developed and the deficiency of personalized methods. The clinical practice is mainly based on a weight dependent dosage of local anaesthetic drugs without any biological gender related considerations.

In other medical specialities (e.g. cardiology, oncology, infectious diseases), there is a worldwide trend towards personalized medicine.^3–6^ For regional anaesthesia purposes, only a few studies investigate with controversial results the possible impact of biological gender differences.^7–12^ Most of these studies did not primarily investigate the impact of biological gender in this context.

In principle, there are three different methods possible with regard to specific studies in the field of regional anaesthesia: patient-, volunteer- or animal- based studies. Our scientific study group (“Regional Anaesthesia and Paediatric Anaesthesia” at the Medical University of Vienna) has extensive experience in the field of volunteer studies.^2,13–16^ Volunteer studies in the field of peripheral regional anaesthesia are associated with the following advantages as compared with clinical studies in patients:

- The entire study period is organized and performed in an environment which is specially designed for volunteer studies.
- The daily practice in a clinical environment (e.g., operation theatre, recovery room, emergency room, etc.) is busy and the particular focus is not on data collection for studies.
- In particular in the field of regional anaesthesia, duration of sensory and motor blocks is difficult to measure due to postoperative swelling, casts, wound-dressings etc.
- Volunteers are more motivated to provide exact data regarding various study related scoring systems as comparted with patients, who are (understandably) more focused on their particular disease / injury.

We therefore designed this prospective, single-centre, volunteer-based study to investigate the impact of biological gender (male versus women) on peripheral nerve blockade. The duration of sensory block is defined as primary outcome parameter. After 2 x 12 cases, we perform an interim analysis.

